### 2.10. Physical Fitness

Muscular strength and cardiovascular capacities will be tested to assess physical fitness.

#### 2.10.1. Muscular Strength

The maximal handgrip strength (in Kg) will be assessed using a hand dynamometer (JAMAR^®^ hand dynamometer, Chicago, IL, USA), as a proxy measure of the general strength (i.e., sarcopenia) [56]. Participants sit on a chair without armrests clenching the hand around a dynamometric handle, they put their hand on their leg to relax the shoulder and to avoid the elbow’s movements. One practice trial is allowed and then, three attempts for each side alternated, with a 30 s rest between, are performed. Only the best of the three trials of each hand is considered for analysis. The strength and fatigue tolerance of the lower limbs is assessed with the Timed-stands test [57]. Participants sit on a chair without armrests placed against a wall to prevent it from moving during the test. The test starts with the participant seated in the middle of the chair, back straight, feet on the floor approximately shoulder-width apart. Arms are crossed at the wrists and held against the chest. At the signal, the participant has to stand up fully (body erect and straight) and then go back to the initial seated position 10 times as fast as possible. The participants are encouraged to complete the repetitions without using their arms. The participant is clearly instructed to be fully seated between each stand. Two repetitions to assess and fully understand the movement are permitted before the test session [57]. The time to complete the 10 repetitions will be recorded.

#### 2.10.2. Cardiovascular Capacities

The 10 m incremental shuttle walking test (SWT) will be assessed to determine the functional capacity of older individuals [58]. It is performed in a 10-m course, identified by two cones placed 0.5 m from each endpoint, with an initial speed of 0.5 m/s, increasing 0.17 m/s every minute. In the present study, the original protocol (12 levels) is slightly modified by extending the test up to 15 levels of 1 min, since only healthy subjects are involved. The walking speed prescribed by a metronome: brief periodic beeps indicate when the participants should be turning around the cone. The test is terminated when participants are unable to cross the cones by the time the signal occurred on three consecutive occasions (i.e., are >0.5 m from the cone), or when they feel too breathless and/or fatigued to continue and/or show signs of physical discomfort (symptoms as dyspnea, dizziness, and vertigo) and/or no longer wish to continue. Verbal instructions are given by examiners when the participants fall behind on the required walking/running speed, providing the participant an opportunity to catch up in the next one. The last completed speed level is considered as the maximal walking speed (Vmax, in km/h). Participants subsequently rate their perceived exertion by using the Borg Scale. The post-exercise HRmax and RPE will be also recorded. Moreover, HR will be measured after 3 min rest, to ensure that participants’ HR relax to pre-exercise levels.

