### 2.12. Sample Size

The sample size calculation was performed using G. Power 3.1.9.7 (Kiel, Germany) [59]. In order to detect relevant between groups differences and in the changes from pre- to post-intervention, we calculated a sample size sufficient to detect medium effect sizes. Therefore, f = 0.25, α = 0.05, *p* = 0.80, were chosen to favor clinically significant effect sizes. To test the main hypotheses of the present study, 42 participants, are required. In order to compensate for possible dropouts, 3 more participants will be included. The three groups are composed of 15 participants each.

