### 3.1. Differences in the Effectiveness of the Three Training Protocols on Cognitive, Physical, and Motor Capacities

In accordance with the literature [60,61], global cognitive performance is expected to be enhanced after training in all three groups. However, it is expected that the CT-c and CT-fit protocols will lead to larger improvements in EF than NW. This should result from the combination of the effects of coordination training and aerobic exercise on cognition [10,15] that is allowed by the synergy between facilitation and guidance effects that occur at the brain level [35,62,63]. Moreover, a strong hypothesis is that CT-fit will be a more effective training protocol to improve EFs [64]. It should be the case since the MwT training conditions used in the CT-fit require the implementation of cognition in action, which is closer to real-life situations than TwM task conditions used in the CT-c. Additionally, according to Herold and colleagues [30], MwT training has a higher potential than TwM training to stimulate brain plasticity, due to the multiple sensory systems activated and involved [30]. In summary, one could expect that the CT-fit will show larger benefits for executive function as compared to the other groups. Nevertheless, the two other forms of training are also predicted to lead to improvements in EFs. In addition, due to the presence of specific DT exercises in the CT-c, participants in this training protocol will show better dual-task performance in the related tests. The question remains, however, of the possible benefits of the other protocols on DT performance. This issue will be addressed. Finally, visuospatial capacities are expected to be more improved by the CTs, especially by the CT-fit due to the embodied characteristics, than in NW. Indeed, it has been previously demonstrated that coordination training specifically impacts visuospatial capacities [12,14]. With respect to physical fitness, reflected by cardiovascular capacities, in accordance with [name] and colleagues’ [27] study, it is expected that all three groups will improve their cardiovascular capacities. This could occur if the mean level of effort, indexed by mean heart rate calculated during the different sessions for the three training programs, is roughly equivalent [27]. If not the case, a difference could be observed between the three groups in the relative test. In case of differences between the three groups, we will analyze heart rate and data from the Borg scale to determine whether one of three training protocols was (at least perceived) of higher intensity, relative to the others. Regarding muscular capacities, it is expected that the two CTs will show a significant improvement in the related tests, larger than those observed in NW. Motor fitness is expected to be impacted by the three training programs, as previously observed by [name] and collaborators [27]. However, one expects that the two CTs should be more effective than NW in this respect. Indeed, presumably, NW requires the repetition of automated arm-leg coordination (stabilization by quantitative repetition), while the CT programs allow developing whole-body and multi-limb coordination through a variety of different exercises, which may be learned over the different sessions and could allow qualitative incorporation of new behavioral patterns in the repertoire of existing ones. Thus, NW and CTs are hypothesized to develop motor fitness and coordination capacities [27], while differently, due to the respective part of repetitive practice of automated movements, variety and novelty of the to be learned coordinated movements. In addition, one expects to observe an improvement in walking speed (cm/sec), in the single task in the NW group relative to the CT groups. Additionally, a decrease in the size of the base of support (cm) is expected more for the CTs groups, proving the effectiveness of the specific balance training proposed in these training groups. Finally, as in our previous study, the percentage of responders (i.e., participants who progressed in the exercise under interest) will be also assessed to check whether it is higher for some protocols, though differentially for specific tests. In the lack of related studies available in the literature, no hypothesis is made in this respect but these analyses could help to interpret eventual differences of performance between groups and tests.

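### Scoring the shuttle walk by the last completed one-minute level leaves mean gains unbiased but adds avoidable noise and distorts the responder percentage

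*Protocol article*

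**What the plan says.** The test in Section 2.10.2 runs over a 10 m course "with an initial speed of 0.5 m/s, increasing 0.17 m/s every minute". The authors modify the original 12 levels by "extending the test up to 15 levels of 1 min". The scoring rule is explicit: "The last completed speed level is considered as the maximal walking speed (Vmax, in km/h". The section describes no credit for a partly completed level, no shuttle count and no distance. It adds that "The post-exercise HRmax and RPE will be also recorded", and heart rate is measured again after three minutes' rest, but Vmax is the only performance score defined for cardiovascular capacity.

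Section 3.1 attaches a hypothesis to this outcome: "it is expected that all three groups will improve their cardiovascular capacities". It gives no expected size of gain. The same section plans to compare, across programmes, the percentage of responders, meaning participants who progressed on a given test. It makes no prediction for that comparison and does not list the tests involved.

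Section 2.12 sizes the trial with "f = 0.25, α = 0.05" and power 0.80, and concludes that "42 participants, are required". Three more are added for dropout, giving 15 per group. Section 2.13 analyses those who complete all pre- and post-tests, by repeated measures ANOVA.

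**The concern.** Around 7 km/h a level holds about 12 shuttles of 10 m. A participant who stops after the first shuttle of a level and one who stops after the eleventh get the same Vmax. A gain of several shuttles inside one level is recorded as no change, while a gain of one shuttle across a boundary is recorded as 0.612 km/h.

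Two things are at stake. The first is the precision of the only cardiovascular performance score, in a trial with 15 participants per group and little slack beyond the dropout allowance. The second is the responder percentage. It counts individuals who moved in the right direction, so it is sensitive to how coarse the scale is in a way that a mean is not.

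**Working it through.** **The plan's own figure.** For the group-by-time interaction with 3 groups, m = 2 measurements and an assumed correlation of 0.5 (not stated in the article), the noncentrality is λ = f²·N·m/(1 − ρ) = 0.0625 × 42 × 2/0.5 = 10.5. With 2 and 39 degrees of freedom, power is 0.803; at N = 39 it is 0.769. The stated 42 is reproduced.

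**Step and resolution (from Section 2.10.2).** 0.17 × 3.6 = 0.612 km/h per level. Level 10 is 0.5 + 9 × 0.17 = 2.03 m/s = 7.31 km/h, or 2.03 × 60/10 = 12.2 shuttles per minute. Counting shuttles would therefore resolve about 0.612/12.2 = 0.05 km/h.

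**Rounding error.** SD per test = 0.612/√12 = 0.177 km/h. SD on a change = 0.177 × √2 = 0.250 km/h.

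**Mean gain.** Take a person with a fixed gain g below one step whose starting point is equally likely to lie anywhere within a level. The chance of crossing a boundary is g/0.612, and crossing scores 0.612, so the expected observed gain is (g/0.612) × 0.612 = g. The chance of no visible change is 1 − g/0.612: 51% at 0.3 km/h and 18% at 0.5 km/h. Those who cross make up exactly for those who do not.

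**Variance, power and responders.** Assumptions: mean Vmax 7 km/h, mean gain 0.3 km/h, between-person SD 0.7 to 1.5 km/h, pre/post correlation 0.5 to 0.9. None of these is given in the article.
- SD of the true change = SD × √(2(1 − ρ)).
- Variance ratio = 1 + 2 × (0.612²/12)/(SD of change)².
- True improvers = Φ(0.3/SD of change).
- Power = power at λ = 10.5/ratio, for an interaction that unrounded scores would detect with 80% power at N = 42.
- Apparent improvers and zero change come from simulation with 1,000,000 draws per row, rounding down at both visits.

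| SD | ρ | SD of change | Variance ratio | Power | True improvers | Apparent improvers | Zero change |
|---|---|---|---|---|---|---|---|
| 0.7 | 0.5 | 0.70 | 1.13 | 75% | 67% | 50% | 30% |
| 0.7 | 0.9 | 0.31 | 1.64 | 58% | 83% | 49% | 46% |
| 1.0 | 0.5 | 1.00 | 1.06 | 78% | 62% | 50% | 23% |
| 1.0 | 0.7 | 0.77 | 1.10 | 76% | 65% | 50% | 28% |
| 1.0 | 0.9 | 0.45 | 1.31 | 68% | 75% | 50% | 40% |
| 1.5 | 0.5 | 1.50 | 1.03 | 79% | 58% | 50% | 16% |
| 1.5 | 0.9 | 0.67 | 1.14 | 75% | 67% | 50% | 31% |

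The simulated mean gain was 0.30 km/h in every row. At SD 1.0, restoring 80% power would take about 42 × 1.06 = 45 to 42 × 1.31 = 55 participants.

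The near-constant 50% has a simple cause. To show progress a participant must on average gain about half a step, 0.612/2 = 0.306 km/h, and the assumed mean gain sits almost on that point. Another mean gain would give another apparent percentage. The general effect is that the bar for being a responder moves from zero to roughly 0.3 km/h.

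**The case against.** The strongest reply is that level scoring is explicit, objective and identical at both visits and in all arms, and that it contradicts nothing in the article. That stands: this is a choice of measurement that could be better, not an error.

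A reader might infer that most of a moderate gain is rounded away. The arithmetic does not support it. Individual gains are misrecorded in both directions, and they cancel in the mean as long as true speeds are spread over several levels.

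The size of the loss rests on assumption. With SD 1.0 and the correlation of 0.5 that reproduces the plan's 42, power falls only from 80% to 78%. Larger losses need more homogeneous or more repeatable scores, which the article neither shows nor rules out.

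A reader might also infer that a missed shuttle-walk difference would leave training intensity unexamined, because Section 3.1 makes the heart-rate and Borg analysis follow from a group difference. But Section 2.7 plans the heart-rate analysis without that condition, and Section 2.6 monitors heart rate in every session. If a non-significant difference were read as equal gain, the fault would lie in that inference rather than in the score.

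Nor does the article say that shuttle counts go unrecorded. It only leaves them out of the score. Finally, the outcome is secondary to the cognitive question, the expected improvement in all three groups draws on the whole sample, and no hypothesis is attached to the responder percentage. All of this lowers the weight of the point without removing it.

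**Conclusion.** The point holds as a minor, avoidable loss of information. Vmax in whole levels gives unbiased mean gains and group differences, with an added error SD of 0.25 km/h on each change. That is about 3% to 64% more variance of the change over the assumed range, and 6% to 31% at SD 1.0 km/h. The documents cannot narrow this range because they give no SD, correlation or expected gain for Vmax.

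The clearer consequence is for the responder percentage, if it is computed for the shuttle walk. Under an assumed mean gain of 0.3 km/h, true improvement in 58% to 83% of participants is displayed as about 50%. Groups with the same mean gain but different true responder rates would then look alike. The conclusions on the cognitive outcomes are untouched.

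**What to change.** Keep the test and its stopping rules as they are. In Section 2.10.2:

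- Record the number of shuttles completed up to the end of the test.
- Fix in advance one counting rule for missed beeps. It is needed because a participant may miss a signal and catch up, and because the test can end in several ways.
- Use as the shuttle-walk outcome either total distance in metres or an interpolated Vmax = speed of last completed level + 0.612 km/h × (shuttles completed in the unfinished level / shuttles in that level).
- Use the same score for the responder percentage in Section 3.1, and still report the last completed level.

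The cost is one extra number on the record sheet, a wording change, and slightly less direct comparability with studies scored by level, which reporting the level largely offsets. The change has to be in place before testing starts, since shuttles that were not counted cannot be recovered later.

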### 2.11. Data Management

The included participants will be registered with an identification number, and all the data collected will be anonymized. Data will be collected and saved on a separate hard disk and treated anonymously or, for each identification code, a logbook will be started in which test results from baseline and post-intervention assessments will be collected as well as the documentation on each training session. In terms of data quality, a trained project-assistant will verify the data entries and check the digitalized version after all training and assessments are finished.

### 2.12. Sample Size

The sample size calculation was performed using G. Power 3.1.9.7 (Kiel, Germany) [59]. In order to detect relevant between groups differences and in the changes from pre- to post-intervention, we calculated a sample size sufficient to detect medium effect sizes. Therefore, f = 0.25, α = 0.05, *p* = 0.80, were chosen to favor clinically significant effect sizes. To test the main hypotheses of the present study, 42 participants, are required. In order to compensate for possible dropouts, 3 more participants will be included. The three groups are composed of 15 participants each.

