### 2.13. Statistical Analysis

Data will be analyzed with SPSS (SPSS Inc., Chicago, IL, USA). The statistical analysis will allow us to determine the effects of the three different training programs on the cognitive, motor, and physical variables. The analysis will include subjects who completed all the pre- and post-tests. Data of the pre-test and post-test will be presented using descriptive statistics: mean, standard deviation, and percentage to describe the participants’ characteristics and performance on assessments. Comparisons within and between groups at baseline and post-intervention will be done using repeated measures ANOVA, and Newman-Keuls tests as post hoc analyses. The global Anova carried out between groups will allow testing the existence of a training effect (pre/post) for the different groups. Training is expected to improve performance for the three groups for both cognitive and physical variables.

With respect to the post-comparisons, we predict that no statistical differences should be observed between groups in the pre-test, while differences should be observed in the post-test. Specifically, post-hoc comparisons of the performance in the post-test should allow determining whether, as predicted, CT-fit training leads to greater benefits than the two other training modalities.

Baseline differences between groups will be carried out by observing the % of progress (pre/post-training) in each group, in some relevant measures. Adherence to programs will be measured by the absence rate (in %).

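### The 80% power claimed for 42 participants fits the omnibus group × time interaction, not the post-test comparisons that decide whether CT-fit beats both other programs

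*Protocol article*

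**What the plan says.** Protocol article, section 2.12, gives the inputs as "f = 0.25, α = 0.05, *p* = 0.80" (the last is evidently power) and describes the result with "we calculated a sample size sufficient to detect medium effect sizes". The effects in view are differences between groups and changes from before to after training. It then says "To test the main hypotheses of the present study, 42 participants, are required", adds 3 for dropout, and sets 15 per arm. Neither the G*Power test nor the pre/post correlation is given.

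The Aims and Hypotheses section predicts that CT-fit will give higher executive benefits than both NW and CT-c. Section 2.13 plans a repeated measures ANOVA with Newman-Keuls tests afterwards, analyses completers only, and says how this prediction is settled: "post-hoc comparisons of the performance in the post-test should allow determining whether, as predicted, CT-fit training leads to greater benefits" than the other two programs.

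**The concern.** The power statement is attached to the main hypotheses and to medium differences between groups. The hypothesis about CT-fit is settled by a different procedure from the one that returns 42: a joint requirement that CT-fit exceed each of two arms on post-test scores, tested stepwise. If the 80% does not carry over to that step, the article credits the trial with more sensitivity on its central question than it has. A non-significant CT-fit versus CT-c comparison would then appear to come from a trial with 80% power when it may say little either way.

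**Working it through.** **Inputs.** From 2.12: f = 0.25, α = 0.05, power 0.80, N = 42, so 14 per arm. From 2.13: 3 groups, m = 2 times, Newman-Keuls on post-test scores. Assumed, because the article does not give them: the pre/post correlation ρ, equal SDs, equal baselines and the pattern of the three means.

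**Step 1: reproduce 42.** For the omnibus interaction, λ = f²·N·m/(1 − ρ). With ρ = 0.5, λ = 0.0625 × 42 × 2 / 0.5 = 10.5 on 2 and 39 df, and power is 80.3%. With groups of equal size, 42 is the smallest N that reaches 80%. The result depends on ρ:

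| ρ | Power at N = 42 | N for 80% |
|---|---|---|
| 0 | 49% | 81 |
| 0.3 | 65% | 60 |
| 0.5 | 80% | 42 |
| 0.7 | 96% | 27 |

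**Step 2: other tests of group differences at f = 0.25.**
- Between-group effect of the repeated-measures model, λ = f²·N·m/(1 + ρ) with ρ = 0.5: λ = 5.25/1.5 = 3.5; power 34% at 42; N = 120 needed.
- One-way F test on the post-test, λ = f²·N = 2.625: power 27% at 42; N = 159 needed.

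So the 80% belongs to the interaction.

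**Step 3: what f = 0.25 means on the post-test.** There are two readings.
- Reading A: f = 0.25 is the post-test between-group effect.
- Reading B: f = 0.25 is the interaction effect that yields 42. On change scores this is f = √(λ/N) = √(10.5/42) = 0.50. At ρ = 0.5 the SD of change, √(2(1 − ρ)), equals 1 SD of the score, so with equal baselines the post-test f is also 0.50.

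If CT-fit lies D above two equal arms, f = D·√2/3 = 0.4714·D. Reading A gives D = 0.25/0.4714 = 0.53 SD and reading B gives D = 0.50/0.4714 = 1.06 SD. If the three means are evenly spaced with CT-fit highest, the extreme pair differs by f·√6, which is 0.61 SD (A) or 1.22 SD (B), and adjacent pairs by half of that.

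**Step 4: power of the deciding step, 14 per arm.** The single-pair figures use the noncentral t, two-sided and unadjusted. The joint figures come from simulating Newman-Keuls on the three post-test means (critical studentized ranges 3.45 for three means and 2.86 for two, 39 df).

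| | One unadjusted pair | CT-fit beats both |
|---|---|---|
| A, two equal arms (0.53 SD) | 28% | 12% |
| A, evenly spaced | 12% adjacent, 35% extreme | 7% |
| B, two equal arms (1.06 SD) | 78% | 64% |
| B, evenly spaced | 35% adjacent, 88% extreme | 34% |

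If all 45 complete, the joint figures become 8–14% (A) and 36–69% (B).

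**Step 5: detectable difference.** One unadjusted post-test contrast with 14 per arm and 39 df reaches 80% power at 1.09 SD. Adjusting for baseline multiplies this by √(1 − ρ²): 1.086 × √0.75 = 0.94 SD at ρ = 0.5, and 1.086 × √0.51 = 0.78 SD at ρ = 0.7.

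**The case against.** The best defence is that 42 is correct for what was probably calculated. The target wording in 2.12, group differences together with pre-to-post change, describes a group × time interaction, and 2.13 plans the matching repeated measures ANOVA. Sizing on the omnibus test and following it with post hoc comparisons is common, and nothing in 2.12 attaches 80% to the post hoc step by name. The main hypotheses also include circuit training against NW, not only CT-fit against both. At the 1.06 SD implied by the calculation, one unadjusted pairwise test has 78% power, close to the claim. Leaving the G*Power option and the correlation to a fuller document is normal for a condensed article.

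Much of this stands. A reader might infer that 42 is an arithmetic error, or that power on the main question is simply 12–28%. The documents support neither. The stated inputs give 42 at ρ = 0.5, and figures that low arise only if f = 0.25 is taken as the post-test effect, which is not the effect that produces 42. The missing correlation is not a fault in itself; it matters because the 80% depends on it. Nor does the article set any rule for reading a null result, so one cannot say that it would be taken as evidence against CT-fit.

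The defence does not rescue the claim as written. CT-fit superiority is among the main hypotheses, 2.13 says how it is decided, and beating both arms falls short of 80% in every case worked out above. The interaction reading saves the number 42 only by making the pairwise difference about 1.06 SD, and then the medium label fails.

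**Conclusion.** The point holds in a limited form. The stated power is right for the omnibus interaction at ρ = 0.5 and wrong as a statement about the comparison that decides the CT-fit hypothesis. Power for CT-fit beating both arms with 14 per arm is about 7–12% if the medium effect is a post-test f of 0.25, and about 34–64% if it is the interaction f of 0.25. The article does not settle which is meant, so both must be reported. The lower end of each range is for evenly spaced means and the upper end for CT-fit above two equal arms.

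These figures assume equal SDs, equal baselines and 42 completers; reading B also takes ρ = 0.5 as the value behind the 42. The correction is needed because the power claim concerns the trial's central question and does not hold for it. It does not follow that N must increase or that the planned model is unsuitable.

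**What to change.** Keep N = 45 and restate section 2.12:
- 42 participants give 80% power for the omnibus group × time interaction at f = 0.25, assuming a pre/post correlation of 0.5. This is equivalent to CT-fit out-gaining two equal arms by about 1.06 SD. If a different correlation was used, state it.
- Remove "we calculated a sample size sufficient to detect medium effect sizes" as a claim about the between-group comparisons.
- With 14 per arm, a single unadjusted post-test contrast has 80% power only at about 1.09 SD (about 0.94 SD baseline-adjusted at correlation 0.5, 0.78 SD at 0.7), and power for CT-fit beating both arms is below 80%.
- In 2.13, say that non-significant contrasts will be reported with confidence intervals and described as inconclusive.

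The cost is wording only. The downside is that the stated sensitivity becomes less favourable.
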